#### 2. Per-Protocol Analysis

A sensitivity analysis on the primary outcome has been carried out on a per-protocol basis to examine robustness of conclusions to different assumptions about departures from randomised policies. The target intervention exposure was 3 aerobic sessions per week, completed on separate days, for 16 weeks, with a compliance threshold set at 80%; equivalent to ≥ 39 independent aerobic exposures with no greater than 2 weeks between exposures. Before recruitment commenced a compliant session was defined as a supervised exercise session, but during the course of the trial this definition was relaxed to include unsupervised sessions captured using the activity monitor. The same mixed model was used for the primary outcomes accounting for person random effects, baseline (as a continuous covariate) and 4-month blood pressure values (or peak oxygen uptake), gender, age (<24, 24–29, >30 years old), and gestational age (<32, 32-37, >37 weeks) as fixed effects with treatment by 16 week time point interaction also included was used to analyse 24 Hour Awake Ambulatory Blood Pressure (Systolic and Diastolic) on the per-protocol population. The results are presented in eTable 3, nonparametric 95% confidence intervals around the unadjusted mean difference and p-values are not presented. The results from the per-protocol analysis reinforce the interpretation of the main trial results: that there is no difference between the Control and Exercise Intervention groups in 24 Hour Awake Ambulatory Blood Pressure at 16 or 52 weeks post-randomisation.

3. Subgroup Analysis

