**5. TABLES**

| Quantiles | Systolic Blood Pressure |  | Diastolic Blood pressure |  |
| --- | --- | --- | --- | --- |
|  | Intervention | Control | Intervention | Control |
| 30 | 120 | 121 | 72 | 71 |
| 40 | 124 | 124 | 74 | 72 |
| 50 | 125 | 126 | 75 | 75 |
| 60 | 129 | 128 | 76 | 77 |
| 70 | 131 | 130 | 80 | 79 |

eTable 1. This table shows the values imputed for each quantile for both Systolic and Diastolic Blood Pressure for the first sensitivity analysis.

eTable 2. Sensitivity analysis using MICE

|  | Exercise Intervention | | Control | | Mean Difference (95%) | |
| --- | --- | --- | --- | --- | --- | --- |
|  | n | Mean (SD) | n | Mean (SD) | Unadjusted | Adjusted |
| **24 Hour Awake Ambulatory Systolic Blood Pressure** | | | | | |  |
| Baseline | 102 | 129.1 (9.3) | 101 | 128.3 (8.7) | - | - |
| 16 Weeks | 102 | 126.6 (11.3) | 101 | 126.0 (10.0) | 0.6 (0,1) | 0.0 (-2.6,2.7) |
| **24 Hour Awake Ambulatory Diastolic Blood Pressure** | | | | | |  |
| Baseline | 102 | 77.0 (6.4) | 101 | 77.4 (7.5) | - | - |
| 16 Weeks | 102 | 76.4 (6.9) | 101 | 75.6 (6.7) | - 1. (0,1) | 1. (-0.9,2.9) |

eTable 3. Per-protocol analysis

|  | Exercise Intervention | | Control | | Mean Difference (95%) | |
| --- | --- | --- | --- | --- | --- | --- |
|  | n | Mean (SD) | n | Mean (SD) | Unadjusted | Adjusted |
| **24 Hour Awake Ambulatory Systolic Blood Pressure** | | | | | | |
| Baseline | 82 | 129.41 (9.46) | 101 | 128.25 (8.68) | - | - |
| 16 Weeks | 71 | 126.93 (11.58) | 84 | 125.83 (10.00) | 1.10 | 0.02 (-2.87,2.92) |
| 52 Weeks | 63 | 127.81 (13.11) | 69 | 125.52 (11.82) | 2.30 | 1.52 (-1.61,4.65) |
| **24 Hour Awake Ambulatory Diastolic Blood Pressure** | | | | | | |
| Baseline | 82 | 77.48 (6.19) | 101 | 77.36 (7.46) | - | - |
| 16 Weeks | 71 | 76.51 (7.04) | 84 | 75.54 (6.73) | 0.97 | 0.61 (-1.41,2.64) |
| 52 Weeks | 63 | 77.01 (8.32) | 69 | 75.24 (7.76) | 1.77 | 1.31 (-0.88,3.49) |

eTable 4. Subgroup comparison of 24 Ambulatory Blood Pressure (mmHg) and Peak Oxygen Uptake (ml/kg/min) according to Volume of Weekly Supervised Exercise Completed.

|  | Exercise Intervention | | | Control | | Mean Difference (95%) | | | |
| --- | --- | --- | --- | --- | --- | --- | --- | --- | --- |
|  | n | Mean (SD) | | n | Mean (SD) |  | | | Adjusted |
| **24 Hour Awake Ambulatory Systolic Blood Pressure** | | | | | | | |  | |
| **Weekly Exercise Supervision ≥ 3 hours** | | | | | | | | | |
| Baseline | 45 | 129.6 (9.0) | | 101 | 128.3 (8.7) |  | | | |

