# STATISTICS AND ANALYSIS

## Description of Statistical Methods

The analysis will be carried out on the basis of intention-to-treat (ITT). This is, after randomisation, participants will be analysed according to their allocated intervention group irrespective of what they actually receive.

Patient demographic characteristics and other baseline information will be summarised by treatment group. Numbers (with percentages) for binary and categorical variables and mean (standard deviation), or median (interquartile or full range) for continuous variables will be presented. Normality of variables will be assessed by visual assessment of the normality curves and the Shapiro-Wilk test. The analysis of the primary outcome will be assessed using analysis of covariance (ANCOVA) adjusting for baseline values and minimisation factors used in the randomisation process. Results will be presented as adjusted mean difference in change in ambulatory blood pressure between randomised groups at 4 months with 95% confidence intervals (CI) and associated two-sided p value. The analysis of secondary outcomes will also be done using analysis of covariance (ANCOVA) to establish a co-variant model to examine the effect of cardiac structure, vascular function and lifestyle behaviours on exercise capacity. Outcomes measured on more than one occasion will be analysed using a mixed effects model. The data collected from the sub-study will be analysed using paired and independent T-test. If the model assumptions are not met and evidence of departure from Normality is observed, transformations of the data will be employed or non-parametric tests will be carried out. Statistical analysis will be carried out using STATA or SPSS statistical software.

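### The per-protocol mixed model appears to use one common variance at 16 and 52 weeks although the raw SDs are 16-17% larger at 52 weeks, so eTable 3's 52-week intervals are probably somewhat too narrow and its 16-week intervals somewhat too wide

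*Supplement*

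**What the plan says.** Protocol section 11.1 (Description of Statistical Methods) names ANCOVA, adjusted for baseline and the minimisation factors, for the primary outcome at 4 months. For repeated outcomes it adds: "Outcomes measured on more than one occasion will be analysed using a mixed effects model". It gives no covariance structure. Section 11.3 leaves the detail to a separate statistical analysis plan, which is not shown.

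Section 2 of the supplement describes the model behind eTable 3: "The same mixed model was used for the primary outcomes accounting for person random effects". Its list of terms includes "baseline (as a continuous covariate) and 4-month blood pressure values", then sex, age and gestational age, "as fixed effects with treatment by 16 week time point interaction also included". It mentions no residual structure or visit-specific variance.

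eTable 3 reports the result for each visit. For systolic pressure the rows read "16 Weeks | 71 | 126.93 (11.58) | 84 | 125.83 (10.00) | 1.10 | 0.02 (-2.87,2.92" and "52 Weeks | 63 | 127.81 (13.11) | 69 | 125.52 (11.82) | 2.30 | 1.52 (-1.61,4.65" (intervention n, mean and SD; control n, mean and SD; unadjusted difference; adjusted difference with 95% limits).

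**The concern.** A random person effect plus a single residual variance gives every visit the same conditional variance. If blood pressure is more variable at 52 weeks, the model averages the two variances. The standard error is then too small at 52 weeks and too large at 16 weeks.

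Section 2 concludes that the arms do not differ at either time. For a null conclusion the interval width is the evidence, because it shows which effects are excluded. An interval that is too narrow at 52 weeks excludes more than the data allow.

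The wording adds a smaller problem. It places 4-month blood pressure, which is the 16-week outcome, next to the baseline covariate, so the model cannot be rebuilt with certainty from the text.

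**Working it through.** **Inputs.** All are from eTable 3. The numbers analysed are 71 and 84 at 16 weeks (155) and 63 and 69 at 52 weeks (132).

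**1. Raw pooled SDs.** Formula: sqrt{[(n1−1)SD1² + (n2−1)SD2²]/(n1+n2−2)}.
- Systolic, 16 weeks: sqrt[(70×11.58² + 83×10.00²)/153] = 10.75.
- Systolic, 52 weeks: sqrt[(62×13.11² + 68×11.82²)/130] = 12.45. Ratio 1.158.
- Diastolic, from SDs of 7.04/6.73 and 8.32/7.76: 6.87 and 8.03. Ratio 1.169.

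**2. Conditional SD implied by each reported interval.** Formula: (half-width/1.96)/sqrt(1/n1+1/n2). The root is 0.1612 at 16 weeks and 0.1743 at 52 weeks. In a random-intercept model this approximates the total conditional SD (person plus residual).

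| | Half-width | Implied SD |
|---|---|---|
| Systolic, 16 weeks | 2.895 | 9.16 |
| Systolic, 52 weeks | 3.130 | 9.16 |
| Diastolic, 16 weeks | 2.025 | 6.41 |
| Diastolic, 52 weeks | 2.185 | 6.40 |

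**3. One variance or two?** The reported 52/16-week half-width ratios are 3.130/2.895 = 1.081 and 2.185/2.025 = 1.079. A common variance predicts 0.1743/0.1612 = 1.081 from sample size alone. Visit-specific SDs in the raw ratio predict 1.081×1.158 = 1.25 and 1.081×1.169 = 1.26. The reported ratios match the common variance.

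Could the conditional SDs really be equal? The covariates would then have to explain 1−(9.16/10.75)² = 27% of the systolic variance at 16 weeks but 1−(9.16/12.45)² = 46% at 52 weeks. For diastolic the shares would be about 13% and 37%. Baseline would have to predict the later visit much better than the earlier one, which is unlikely.

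**4. Size, if the conditional ratio r equals the raw ratio.** The common variance is taken as the average of the two visit variances weighted by n. Reported over correct width is then F = sqrt[(155+132r²)/287] at 16 weeks and F/r at 52 weeks.
- Systolic, r = 1.158: F = 1.076 and F/r = 0.929. The 16-week interval is 7.6% too wide and the 52-week interval 7.1% too narrow. Coverage at 52 weeks is 2Φ(1.96×0.929)−1 = 93.1%.
- Diastolic, r = 1.169: F = 1.081 and F/r = 0.925. The interval is 8.1% too wide at 16 weeks and 7.5% too narrow at 52 weeks. Coverage at 52 weeks is 93.0%.

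Approximate intervals with the centres held fixed:

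| | Reported | Visit-specific variance |
|---|---|---|
| Systolic, 16 weeks | −2.87 to 2.92 | −2.67 to 2.72 |
| Systolic, 52 weeks | −1.61 to 4.65 | −1.85 to 4.89 |
| Diastolic, 16 weeks | −1.41 to 2.64 | −1.26 to 2.49 |
| Diastolic, 52 weeks | −0.88 to 3.49 | −1.06 to 3.67 |

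**5. Uncertainty in the ratio.** Treating the visits as independent, the 95% interval for the systolic SD ratio is about 0.98 to 1.37.
- r = 0.98: F/r = 0.991/0.98 = 1.01, so the 52-week interval is about 1% too wide.
- r = 1.37: F/r = 1.185/1.37 = 0.86, so it is about 14% too narrow.

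**6. Simulation.** The runs (2,000 per setting) used eTable 3's sample sizes and assumed a conditional SD of 8.5 at 16 weeks, a ratio of 1.158 and a conditional correlation of 0.3 to 0.7. The random-intercept standard error was 5-8% too large at 16 weeks (coverage about 96-97%) and 6-9% too small at 52 weeks (coverage about 92-93%). The 52/16-week standard-error ratio was 1.04 to 1.07 with a common variance and 1.20 to 1.24 with an unstructured covariance. The reported 1.08 lies near the first range.

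**The case against.** **The variance difference is not established.** It compares raw SDs from samples of 155 and then 132. The systolic test gives p of about 0.08 with visits treated as independent, and 0.02 to 0.08 for an assumed correlation of 0.7 to 0.4. The model's variance is conditional on baseline, and its ratio by visit is not reported. This stands, and it is why the size is given as a range. One cross-check points the same way. The multiple-imputation interval at 16 weeks in eTable 2 (half-width 2.65) implies a systolic SD of about 8.5 if 76 and 84 complete cases are assumed, below 9.16. It is weak evidence, because the population differs and the limits are rounded to 0.1.

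**The primary result is not shown to be affected.** A reader might infer that the primary 16-week interval is too wide. The documents do not support that as a fact. Every interval used here is from a per-protocol sensitivity analysis, and no intention-to-treat primary table is in the supplement. A 16-week ANCOVA, as section 11.1 names, would not have this fault. The only link is section 2's remark that the same model served the primary outcomes. Nor does the fault carry over to eFigures 1 to 4, which the text attributes to ANCOVA on imputed data, multiple imputation and a linear model.

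**The 4-month covariate may be only garbled wording.** A reader might infer that the 52-week effect was adjusted for a post-randomisation outcome. eTable 3 gives 16-week pressure its own adjusted effect, so it was an outcome there. The sentence needs rewording, but it is no evidence of bias.

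**The protocol may properly leave covariance structure to the analysis plan.** That is so. The point is about the model as described and reported in the supplement, not the protocol's silence.

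**Conclusion.** The point holds for eTable 3. The reported widths fit one common variance at both visits for both pressures, while the raw SDs are 16-17% larger at 52 weeks. The common variance is inferred from the random-effect description and the interval widths; the text does not state it.

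The best estimate is that the 52-week intervals are about 7% too narrow, with coverage about 93%, and the 16-week intervals 7-8% too wide. This assumes that the conditional SD ratio is near the raw ratio. Over the systolic range of 0.98 to 1.37, the 52-week error runs from about 1% too wide to 14% too narrow.

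The practical effect is small. At the best estimate the limits move by at most about 0.24 mmHg (3.37 against 3.13), all four intervals still include 0, and all still exclude the 5 mmHg reduction used in the sample-size section. The primary 16-week comparison is affected only if its reported interval was taken from this mixed model.

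**What to change.** - Fit the 16- and 52-week values as outcomes with an unstructured covariance, so that each visit has its own variance. Fixed effects: arm, visit, arm-by-visit, baseline, baseline-by-visit and the minimisation factors.
- Refit eTable 3, and any primary table that used this model. State which model, ANCOVA or mixed model, gave the primary 16-week result.
- Reword section 2 so that 4-month blood pressure is an outcome and not a covariate, and name the covariance structure.

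The cost is a small change to the model code and a refit. An unstructured covariance for two visits has three parameters against two for a random intercept plus residual, so it adds one, and the baseline-by-visit term comes on top. With 155 and 132 participants that is easily afforded. Point estimates may shift slightly on refitting because follow-up is incomplete.

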The results from this sensitivity analysis using Multiple Imputation by Chained Equations are very similar to the results from the primary analysis. The main, null, result from the study is shown to be a robust result when looking at departures from the MAR assumption and different approaches when handling missing data.

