# BACKGROUND AND RATIONALE

**Early Hypertension**

Hypertension contributes to 9 million annual global deaths^1^. In the United Kingdom, 1 in 4 adults over the age of 25 are hypertensive and the incidence in the 18 to 40 year old population may be increasing^2^. North American population studies report incidence as high as 1 in 5 of the under-40 age group^3^. Targeted early treatment and primary prevention may have significant benefits on future morbidity and mortality. Blood pressure reductions of as little as 2 mmHg may be enough to reduce future stroke risk by 10%^4^. To drive improvement in primary prevention strategies more understanding is required of the effectiveness of lifestyle and behavioural intervention to lower blood pressure in adults with early cardiovascular risk. This includes investigation of the response to intervention in young adults known to have unique cardiovascular phenotypes associated with early life exposures and familial risk. Prevalence of hypertension is higher in young adults with history of preterm birth and exposure to maternal pregnancy complications such as pre-eclampsia^5–8^. Our recent work supports distinct aetiological pathways for this early cardiovascular risk^9^. The differences observed in blood pressure between preterm and full term born groups track from childhood and by early adulthood approach 10mmHg difference in systolic blood pressure, resulting in a 2-3 fold increase risk of early hypertension.^6,10,11^ In the UK 6-12% of the population are born preterm equivalent to 1-2 million young people at risk of early hypertension. This predicted cardiovascular risk burden is supported by our recent analysis of the Raine Western Australia longitudinal birth cohort, which identified that 1 in 3 adults diagnosed with hypertension before the age of 30 had been exposed to pregnancy complications^12^.

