## The Number of Participants

***Primary Outcome 24-hour awake ambulatory blood pressure***

Our systematic review and meta-analysis of randomised control trials identified an average decrease of 5.4mmHg in systolic blood pressure (SBP) post-intervention via supervised exercise in young adults with prehypertension (mean systolic blood pressure at baseline 126 mmHg). The post intervention standard deviation of change was 8.7 mmHg. Our available cross-sectional pilot data suggests that change will be higher in the preterm born participants and participants exposed to maternal hypertension during pregnancy. To calculate the sample size we have been conservative and used an estimated change of 5 mmHg following 4 months of intervention. We have used a SD of 11.3 from the pooled SD for ambulatory systolic blood pressure from our cross-sectional pilot data. To observe a treatment effect on systolic blood pressure of 5mmHg, powered to 80% (p=0.05) requires a total sample size of 164 participants. The SD deviation for the pooled 24 hour awake diastolic blood pressure is 8.3 mmHg. To observe a treatment effect on diastolic blood pressure of 5mmHg, powered to 80% (p=0.05) requires a total sample size of 114 participants. The power calculations for systolic blood pressure are used to determine the final sample size, with adjustment to 200 participants to allow for 18% attrition. To ensure primary objectives for the study are answered the study team may recruit additional participants to replace those who drop out of the study.

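### The per-protocol section concludes no difference in blood pressure from intervals that merely include zero and still allow more than 2 mmHg in favour of control

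*Supplement*

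**What the plan says.** Section 2 of the supplement reports the per-protocol analysis of awake ambulatory pressure, systolic and diastolic together. It says the results reinforce the interpretation of the main trial, namely "that there is no difference between the Control and Exercise Intervention groups in 24 Hour Awake Ambulatory Blood Pressure at 16 or 52 weeks post-randomisation". The same section notes that "nonparametric 95% confidence intervals around the unadjusted mean difference and p-values are not presented", so the adjusted 95% intervals in eTable 3 are the only inferential evidence given there.

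The protocol describes a superiority design. The Number of Participants section states: "To observe a treatment effect on systolic blood pressure of 5mmHg, powered to 80% (p=0.05) requires a total sample size of 164 participants". The Description of Statistical Methods plans the adjusted mean difference at 4 months "with 95% confidence intervals (CI) and associated two-sided p value". The documents shown contain no equivalence margin and no equivalence test.

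The Background and Rationale, under Early Hypertension, remarks: "Blood pressure reductions of as little as 2 mmHg may be enough to reduce future stroke risk by 10" per cent. This is the only place where 2 mmHg appears as an effect size of interest.

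**The concern.** A superiority test that fails to reject zero does not establish that the difference is zero. To claim no difference, the interval has to lie inside a range of differences judged too small to matter, and no such range was set. The sentence therefore claims more than the intervals can carry, at two time points and for two measures at once.

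At stake is what a reader takes from the trial. The intervals support a firm statement that the planned 5 mmHg reduction did not occur. They do not support a statement that the arms are the same. At 52 weeks in particular, differences of several mmHg in favour of control remain open.

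**Working it through.** **1. The design figure.** Inputs from the Number of Participants section: difference 5 mmHg, SD 11.3, 80% power, two-sided 5%.

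Normal approximation: n per arm = 2 × (1.96 + 0.8416)² × 11.3² / 5² = 2 × 7.849 × 127.69 / 25 = 80.2, so 81 per arm, 162 in total. The t-test version gives 81.15, so 82 per arm, 164 in total. This matches the stated 164. With 18% attrition, 164 / 0.82 = 200, also as stated. The trial was sized for 5 mmHg and nothing smaller.

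**2. Direction of the difference.** In eTable 3 the unadjusted systolic difference at 16 weeks is 126.93 − 125.83 = 1.10, exercise minus control. A positive value therefore means higher pressure in the exercise arm and favours control.

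**3. What the intervals contain.** The adjusted results come from eTable 3 (per-protocol) and eTable 2 (multiple imputation). SE = (upper − lower) / (2 × 1.96).

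| Result | n | Estimate (95% CI) | SE | Includes −5? | Includes −2? | Includes +2? |
|---|---|---|---|---|---|---|
| Systolic, 16 wk | 71 v 84 | 0.02 (−2.87, 2.92) | 1.477 | No | Yes | Yes |
| Systolic, 52 wk | 63 v 69 | 1.52 (−1.61, 4.65) | 1.597 | No | No | Yes |
| Diastolic, 16 wk | 71 v 84 | 0.61 (−1.41, 2.64) | 1.033 | No | No | Yes |
| Diastolic, 52 wk | 63 v 69 | 1.31 (−0.88, 3.49) | 1.115 | No | No | Yes |
| Imputed systolic, 16 wk | 102 v 101 | 0.0 (−2.6, 2.7) | 1.352 | No | Yes | Yes |
| Imputed diastolic, 16 wk | 102 v 101 | 1. (−0.9, 2.9) | 0.969 | No | No | Yes |

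The per-protocol comparisons use 71 + 84 = 155 people at 16 weeks and 63 + 69 = 132 at 52 weeks, both below the 164 required for 5 mmHg.

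**4. Reading.** The lowest lower limit in the table is −2.87, so a 5 mmHg reduction is excluded throughout. Every interval reaches above +2. A 2 mmHg reduction is left open only for systolic pressure at 16 weeks, which is the primary time point, and this holds in both the per-protocol and the imputed analysis. The 16-week finding therefore does not depend on who was counted as compliant.

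**5. Power as a side check.** The chance of missing a true 2 mmHg difference at two-sided 5% is 1 − [Φ(2/SE − 1.96) + Φ(−2/SE − 1.96)]. For the per-protocol systolic results this is 73% at 16 weeks and 76% at 52 weeks; for diastolic it is 51% and 57%. With imputation at 16 weeks it is 68% systolic and 46% diastolic. Once the data are in, these figures add little to the intervals, and the conclusion does not rest on them.

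**The case against.** The strongest reply is that this is loose wording and hides nothing. The adjusted intervals are printed in eTable 3, no protocol text claims equivalence, and all four per-protocol estimates are at or above zero, so there is no hint of a missed benefit. That is fair as far as it goes. It keeps the point to one sentence, but it does not make that sentence correct.

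The reply also disposes of several stronger readings that a reader might infer:

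- *That the data would miss a 2 mmHg effect about three times in four.* This fits systolic pressure only. For diastolic pressure, which the same sentence covers, it is about one in two. Three of the four per-protocol intervals in fact exclude a 2 mmHg reduction.
- *That 2 mmHg is the protocol's margin or its smallest important effect.* It is a background remark, worded as a possibility, about reductions and stroke risk. It is not tied to systolic, diastolic or ambulatory pressure, and it says nothing about increases. The stated design effect is 5 mmHg. I use 2 mmHg only as a yardstick.
- *That the missing-data section makes the same error.* It says "The main, null, result from the study is shown to be a robust result", but the rest of that sentence refers to departures from missing at random and to ways of handling missing data. That is a claim of stability across methods, and null is ordinary wording for a superiority test that did not reject.
- *That 5 mmHg is ruled out because the trial had high power for it.* Power rules nothing out. The confidence limits do.
- *That the trial's main conclusion is wrong.* The main-analysis estimates are not in these documents, so this cannot be judged.

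**Conclusion.** The point holds for the concluding sentence of the per-protocol section. No difference is not supported at either time point. The upper limits are 2.92 and 4.65 mmHg systolic, and 2.64 and 3.49 mmHg diastolic, at 16 and 52 weeks. Systolic pressure at 16 weeks also leaves open a reduction of up to 2.87 mmHg. What the intervals do support is that a 5 mmHg reduction is excluded for both measures at both times, and that a 2 mmHg reduction is excluded in three of the four comparisons.

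The conclusion takes the printed adjusted intervals as correct. At 16 weeks it rests on the per-protocol and imputed results. At 52 weeks it rests on the per-protocol results alone, since eTable 2 gives none for that time. The fault lies in interpretation; no model, estimate or design element is in question.

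**What to change.** Replace the concluding sentence of the supplement's Per-Protocol Analysis with a bounded statement, for example:

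*There was no evidence that exercise lowered awake ambulatory blood pressure. The per-protocol intervals exclude the 5 mmHg reduction that the trial was designed to detect. They do not exclude a 2 mmHg systolic reduction at 16 weeks, or differences favouring control of up to 4.65 mmHg systolic and 3.49 mmHg diastolic at 52 weeks.*

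The missing-data section needs no change. No equivalence test should be added, because its margin would be chosen after the intervals were known. All the numbers are already printed, so the cost is one sentence and a somewhat weaker stated conclusion.
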